## Abstract

**Background:**

Medication non-adherence is a complex health care problem. Due to non-adherence, substantial numbers of cardiovascular patients benefit from their medication to only a limited extent. In order to improve adherence, a variety of pharmacist-led interventions have been developed. However, even the most effective interventions achieved only a modest positive effect. To be effective, interventions should be targeted at underlying barriers to adherence, developed in a systematic manner and tailored to specific features of a target group and setting. The current paper describes the design of the Cardiovascular medication non-Adherence Tailored Intervention (CATI) study aimed to evaluate the (cost-)effectiveness of a patient-tailored intervention programme in patients using antihypertensive medication.

**Methods:**

The CATI study is a randomised controlled trial that will be performed in 13 community pharmacies. Patients aged 45–75 years using antihypertensive medication and considered non-adherent according to pharmacy dispensing data, as well according to a self-report questionnaire, are eligible to participate. Patients in the intervention condition will receive a patient-tailored, pharmacist-led intervention programme. This programme consists of a structured interview at the pharmacy to identify patients’ barriers to adherence and to counsel patients in order to overcome these barriers. The primary outcome is self-reported medication adherence measured with the MARS-5 questionnaire. Secondary outcome measures are blood pressure, illness perceptions, quality of life and societal costs. A cost-effectiveness analysis and process evaluation will also be performed.

**Discussion:**

This study will provide insight into the (cost-)effectiveness of a patient-tailored, pharmacist-led intervention programme in non-adherent patients using antihypertensive medication. This intervention programme allows community pharmacists to support their patients in overcoming barriers to adherence and improving medication adherence in a structured and patient-tailored manner. An effective intervention will not only enhance medication adherence, but may also improve health outcomes and decrease health care utilisation and costs.

**Trial registration:**

Netherlands Trial Register (identifier: NTR5017), registered on 2 February 2015.

**Electronic supplementary material:**

The online version of this article (doi:10.1186/s13063-016-1696-3) contains supplementary material, which is available to authorized users.

## Background

The World Health Organisation (WHO) provides evidence-based guidelines for the treatment of a variety of disorders, as specified in both pharmacological and non-pharmacological treatment strategies [1]. These strategies as implemented in numerous national guidelines aim to reduce risks, (co)morbidity and mortality [1, 2]. Due to inadequately following pharmacological treatment plans, i.e. medication non-adherence, a subgroup of patients benefits from their medication to only a limited extent. Medication non-adherence is a complex health care problem and defined as the process by which patients take their medication as agreed upon with their prescriber [3]. Causes of non-adherence are patient-, social/economic-, condition-, treatment- or health care system-related [4, 5].

Pharmacological treatment of hypertension can result in a reduced risk of cardiovascular events such as stroke and myocardial infarction [5, 6]. Unfortunately, adherence to antihypertensive medication is often suboptimal and is associated with negative health outcomes, such as cardiovascular events [7–9], higher risk of hospitalisation [8–10] and increased health care costs [8]. A meta-analysis of data of 376,162 patients from 20 studies assessing adherence by using prescription refill data of seven cardiovascular drug classes revealed an estimated non-adherence rate of 43% [11]. Adherence varies depending on drug class with non-adherence rates ranging from 35% for angiotensin II-receptor blockers to 72% for beta-blockers [12].

In order to improve patients’ adherence to medication, a variety of mostly pharmacist-led interventions has been developed. However, reviews summarising the results of a number of studies on the effectiveness of these interventions revealed that in only half of the studies adherence was significantly improved as compared to usual care and that in only a few studies better treatment outcomes were achieved [13–18]. One likely explanation is that most studies did not use a theoretical framework, crucial for understanding the complexities of adherence behaviour. On top of that, most described interventions did not made an effort to apply a patient-tailored approach for identifying the specific causes or barriers for individual patients [5, 19]. Finally, most studies were targeted at the general population rather than at patients non-adherent with their medication.

For this study, the Self-regulation Theory has been chosen as a foundation of the intervention programme. According to this theory patients seek to understand their illness by developing a representation of the illness, its cause, its effects, how long it will last and whether it can be cured or controlled [20, 21]. These illness and treatment representations guide their health behaviour. For instance, if a patient regards his or her illness or risk factor for an illness as a problem, the patient will perform health-related behaviour aimed to solve the problem, e.g. taking medication [20, 22–25]. However, multiple factors influence adherence behaviour [5] and it should be recognised that in this theory these influencing factors can be mediated by patients’ illness and treatment representations.

The Cardiovascular medication non-Adherence Tailored Intervention (CATI) study aims to evaluate the (cost-)effectiveness of a patient-tailored, pharmacist-led intervention (CATI intervention programme) aiming to overcome barriers and improve antihypertensive medication adherence in comparison to usual care. The intervention programme includes identifying factors that influence patients’ adherence behaviour, discussing patient’s illness and treatment representations and suggesting a plan to overcome barriers and improve medication adherence.

## Methods

The CATI study protocol was approved by the Medical Ethics Committee of the VU University Medical Center, Amsterdam (reference 2015/219). Written informed consent will be obtained from all study participants.

### Study design

A parallel-group randomised controlled trial will be performed in 13 community pharmacies including 156 patients (Fig. 1). Patients will be randomly assigned to the intervention or the control condition. Patients in the intervention condition will receive the CATI intervention programme performed by the pharmacist, in addition to usual care (further described below in 'Control condition'). The effectiveness of the CATI intervention programme will be measured during a 9-month follow-up. See Additional file 1 for an overview of the Standard Protocol Items: Recommendations for Interventional Trials (SPIRIT) 2013 checklist items [26]. See Additional file 2 for the SPIRIT diagram of the trial procedure.

**Fig. 1 Fig1:**
[figure not shown]
Design of the Cardiovascular medication non-Adherence Tailored Intervention (CATI) study

### Study population and setting

Patients will be recruited from community pharmacies located in urban and rural areas in The Netherlands. Participating pharmacies must have a subscription to the Foundation for Pharmaceutical Statistics (SFK), which is developed by the Royal Dutch Pharmacists Association. SFK registers information on dispensing drugs and will be used for the selection of eligible patients. Patients aged 45–75 years using antihypertensive medication and indicating to have hypertension by self-report are eligible to participate. Antihypertensive medication includes beta-blockers, calcium antagonists, diuretics, angiotensin converting enzyme (ACE) inhibitors and angiotensin II-receptor antagonists. Only patients non-adherent with their antihypertensive medication according to pharmacy dispensing data, as well according to a self-report questionnaire, are eligible. Exclusion criteria are the inability to speak, read and write Dutch, and the use of special medication-intake supporting services provided by the pharmacy, i.e. repeat dispensing and pill packaging.

### Inclusion procedure

To be included in the intervention or the control condition a two-step approach will be applied.

#### Step 1

Eligible patients will be identified by a SFK database search which provides information on dispensed medication. For each class of antihypertensive medication SFK calculates a score by dividing the number of covered days by the length of the therapy window. The number of covered days is calculated by summating the days in the therapy window covered by usage periods which are corrected for overlapping supplies. A score lower than 80% is considered non-adherent. SFK provides a list of patients non-adherent in refilling at least one of the classes of antihypertensive medication during the last 6 months. The researcher will check this list in order to prevent selecting patients who are most likely falsely identified as non-adherent due to switching drugs or hospital stay.

#### Step 2

Patients identified as non-adherent in refilling antihypertensive medication will be invited to fill out a questionnaire. This baseline questionnaire includes an Informed Consent Form and the five-item Medication Adherence Report Scale (MARS-5) questionnaire [27]. The MARS-5 questionnaire assesses self-report medication intake behaviour by five questions rated on a five-point scale and ranges from 5 to 25 points. Patients with a score of below 25 points are considered non-adherent.

Patients who are willing to participate and identified as non-adherent with their antihypertensive medication according to pharmacy dispensing data, as well according to the self-report questionnaire, will be included in the study. Patients identified as non-adherent with only one non-adherence measure will not be included. Patients not willing to participate will be asked to fill out a short questionnaire assessing demographic variables and reasons for their nonparticipation.

### Randomisation

To each eligible patient an unique serial number will be assigned. Subsequently, a member of the research team will perform the randomisation process using blocking [28] with a block size of 4, a random cell selection a 1:1 allocation ratio. A list of patients randomised to the intervention or the control condition will be handed to the pharmacist and pharmacy technician, respectively. Blinding of the participants, pharmacists and pharmacy technicians to treatment allocation is not possible due to the nature of the intervention.

### Intervention condition

Patients in the intervention condition will receive the CATI intervention programme in addition to usual care. The programme is a patient-tailored, pharmacist-led, theory-based intervention programme to enhance adherence with the use of antihypertensive medication. It consists of two steps. First, the patients’ barriers to adherence will be identified, and second, tailored information and advice on the identified barriers and specific needs of the patient will be provided. The Self-regulation Theory suggests that patients make an illness and treatment representation which guides their health behaviour. By providing tailored information to the patient regarding the potential risks of high blood pressure and the need for treatment, it is expected to increase patients’ understanding and perceived need to be adherent with their antihypertensive medication. The programme will be executed by the pharmacist and includes two visits to the pharmacy.

#### First consult

The pharmacist invites the patient for a consult in the pharmacy. The consult starts by interviewing the patient using a semistructured interview guide, called the Quick Barrier Scan (QBS). The aim of the QBS is to explore patients’ barriers to adherence to medication assessed by means of 12 questions, for instance concerning knowledge, side effects, forgetfulness, difficulties with medication intake and lack of motivation. Patients will also be asked about their own ideas of intake barriers. Based upon the identified barrier(s) an intervention module will be selected according to the Tailored Intervention Guide (TIG). The TIG provides an overview of five intervention modules aiming to overcome different barriers to adherence. Each assessed barrier in the QBS conforms to an intervention module in the TIG. If no clear barrier can be identified with the QBS, the first intervention module will be conducted. The five intervention modules include: (1) Providing Information, (2) Providing Tools, (3) Dealing with Side Effects, (4) Overcoming Practical Problems and (5) Diminishing Negative Beliefs. Each intervention module consists of three components. During the first component, the patient will be provided with information regarding the representation and potential risks of high blood pressure, the use of antihypertensive medication and living a healthy lifestyle. During the second component, the pharmacist will give the patient tailored advice on overcoming the identified barriers. The content of the second component is different for each intervention module. For instance, possible recommendations of the second intervention module (Providing Tools) are connecting intake with daily recurring activities or the use of a pill box or medication reminder alarm. Recommendations of the third intervention module (Dealing with Side Effects) are to balance patients’ advantages and disadvantages of medication use; whereas examples of recommendations of the fourth intervention module (Practical Problems) are to register a patient for an intake-supporting service, i.e. pill packaging. During the third component, a summary is made from the information and advice discussed by the pharmacist in order to provide the patient with a short overview of the first consult. This overview can be used as an action plan. The intervention programme and materials are partly based upon the promising results of a previous study in which the feasibility of a modular intervention programme in patients with diabetes was evaluated [29]. On top of that, the intervention materials (the QBS and the TIG) were further developed based upon our own research including a systematic literature review and a cross-sectional study (manuscripts in preparation). The systematic review aimed to provide an overview of the factors influencing antihypertensive medication adherence. The cross-sectional study used a questionnaire to assess barriers to adherence in a Dutch population using cardiovascular medication. These results provided a complete overview of potential barriers to medication adherence which should be incorporated in the intervention materials. Lastly, the intervention materials were approved by an expert panel including a pharmacist, a general practitioner and a sociologist.

#### Follow-up consult

Approximately 3 months after the first consult a follow-up consult will be planned with the patient. The purpose of this follow-up consult is to discuss patients’ implementation of and patients’ experiences with the action plan. If needed, the developed action plan of the first consult will be adjusted based upon patients’ experiences.

During the first consult, the follow-up consult and during an additionally planned visit to the pharmacy, patients’ systolic and diastolic blood pressure will be measured with an automatic sphygmomanometer according to a protocol.

### Training

Participating pharmacists will follow a 1-day training session. The training session comprises a theoretical and a practical part. During the theoretical part, background information on medication non-adherence will be discussed and instructions will be given on study design, protocol and intervention materials. An experienced communication lecturer will provide information and instructions on how to communicate with patients. During the practical part, the pharmacists will practise with communication skills and intervention materials in a patient-pharmacist role-playing setting. Before and after the training session the pharmacists will fill out a form to assess the potential improvement of their knowledge and competencies.

### Control condition

Patients in the control condition will receive usual care according to the Dutch guidelines of the Royal Dutch Pharmacists Association [30]. In summary, the care according to these guidelines consist of checking and dispensing of prescribed drugs, providing instructions on medication use, and providing information about intended effects and possible side effects, during first and second dispensing.

### Primary outcome measure

Self-reported medication adherence will be assessed with the MARS-5 questionnaire at baseline and after 3, 6 and 9 months [27]. The MARS-5 questionnaire comprises five statements of adherence-related behaviour rated on a five-point scale, where 1 = ‘always’, 2 = ‘often’, 3 = ‘sometimes’, 4 = ‘rarely’ and 5 = ‘never’. Scores for each item will be summated to give a total score, ranging from 5 to 25 points. A score below 25 points is considered non-adherent. The questionnaire distinguishes intentional non-adherence and unintentional non-adherence. The statements assessing intentional non-adherence are ‘I alter the dose of my medicines’, ‘I stop taking my medicines for a while’, I decide to miss out on a dose of my medicines’ and ‘I take less of my medicines than instructed’. The statement assessing unintentional non-adherence is ‘I forget to take my medicines’. The MARS-5 questionnaire is easy to use and shows to be a valid and reliable tool for measuring patients’ non-adherence to medication across different illnesses including asthma, diabetes and hypertension [27, 31–33]. The internal reliability (Cronbach’s *α*) ranged from 0.67 to 0.90; test-retest reliability (Pearson’s *r*) was 0.97; and concurrent validity (Pearson’s *r*) with the Morisky Medication Adherence Scale [34] was 0.62. The MARS-5 questionnaire was selected because it is a sufficiently-validated and easy-to-use tool. Furthermore, in addition to measuring the extent of non-adherence, it can distinguish between patients with intentional and unintentional medication non-adherence.

### Secondary outcome measures

Secondary outcomes include patients’ attitudes and beliefs towards medication, quality of life (QoL), illness perceptions, costs and systolic and diastolic blood pressure.

#### Attitudes and beliefs towards medication

Patients’ attitudes and beliefs towards medication will be assessed with the specific Beliefs about Medicines Questionnaire (BMQ) [35, 36] at baseline and after 3, 6 and 9 months. The BMQ Specific can be subdivided into the BMQ Specific Necessity and the BMQ Specific Concern. The BMQ Specific Necessity measures the patients’ beliefs of the necessity of taking the medication and the BMQ Specific Concern measures the patients’ concerns about taking medication. Both subscales range from 5 to 25. The BMQ Necessity-Concern differential can be calculated as the difference between the Concern and Necessity subscales. The BMQ specific subscales can be used to categorise patients into four attitudinal groups: accepting (high necessity, low concerns), ambivalent (high necessity, high concerns), indifferent (low necessity, low concerns) and sceptical (low necessity, high concerns). Research shows evidence on good reliability and acceptable validity of the BMQ scales and supports its use as a research tool when investigating patients’ beliefs about medication [35–37]. The internal reliability (Cronbach’s *α*) for both the Concern and Necessity subscales was 0.83. When assessing the validity of the BMQ with the MARS-5, significant predictive correlations were found for both the Concern and Necessity subscales [37]. The measurement of patient’s beliefs about medication is important because it provides insight into the mechanism by which medication beliefs might influence medication adherence.

#### Quality of life

Patients’ QoL will be assessed using both the valid and reliable 12-Item Short Form (SF-12) questionnaire [38] and the valid and reliable EuroQol (EQ-5D-5L) questionnaire [39, 40] at baseline and after 3, 6 and 9 months. The SF-12 questionnaire consists of 12 questions covering eight dimensions of health, i.e. general health perception, physical functioning, limitations due to physical health problems, bodily pain, vitality, social functioning, emotional functioning and general mental health. The eight domains can produce two summary scores for physical health and mental health. The EQ-5D-5L questionnaire is a standardised instrument measuring five health dimensions (mobility, self-care, usual activities, pain/discomfort and anxiety/depression) with five severity levels each [39]. The EQ-5D-5L questionnaire health states will be converted into utility scores using the Dutch tariff [41]. Utility scores reflect the desirability of a health state and are anchored at 0 (‘death’) and 1 (‘perfect health’). Quality-adjusted life years will be calculated by multiplying the utility of a particular health state by the time spent in that health state using the area-under-the-curve method. Transitions between health states are considered linear.

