### Statistical analyses

Descriptive statistics will be used to characterise the study population. Dropout and loss to follow-up will also be described. The effect analyses will be performed according to the ‘intention-to-treat’ and ‘per-protocol’ principles. Linear and logistic mixed-model analyses will be used to assess the effect of the intervention programme by comparing the differences between the intervention and the control conditions. Mixed-model analysis is needed in order to take into account clustering on pharmacy level and repeated measurements in one patient. Adjustments will be made for possible confounders such as gender, age and education level. The researcher will be blinded during data analyses.

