### Economic evaluation

Both a cost-effectiveness analysis and a cost-utility analysis will be performed according to the intention-to-treat principle. Missing cost and effect data will be imputed using Multiple Imputation by Chained Equations (MICE) [47]. To account for the skewed distribution of costs Predictive Mean Matching will be used in the MICE procedure. The number of imputed datasets will be increased until the loss of efficiency is less than 5% [48]. The results of the imputed datasets will be pooled according to Rubin’s rules. Bivariate regression analyses will be used to estimate cost and effect differences while adjusting for potential confounders and maintaining the correlation between costs and effects. Incremental Cost-Effectiveness Ratios (ICERs) will be calculated by dividing the mean difference in total societal costs by the mean difference in effects. Bias-corrected and accelerated bootstrapping with 5000 replications will be used to estimate 95% confidence intervals around cost and effect differences, and to estimate the uncertainty surrounding the ICERs which will be graphically presented on a cost-effectiveness plane [49]. Cost-effectiveness acceptability curves will be estimated in which the probability that the intervention programme is cost-effective in comparison to usual care is plotted on the y-axis, while the willingness-to-pay per incremental unit of effect is plotted on the x-axis [50].

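### QALYs include the baseline EQ-5D-5L utility, but adjustment for unnamed potential confounders does not secure adjustment for that baseline value

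*Protocol article*

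**What the plan says.** Under Quality of life, the article administers the "EuroQol (EQ-5D-5L) questionnaire [39, 40] at baseline and after 3, 6 and 9 months" and obtains QALYs "by multiplying the utility of a particular health state by the time spent in that health state using the area-under-the-curve method". It adds: "Transitions between health states are considered linear".

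Under Economic evaluation, bivariate regression is used "to estimate cost and effect differences while adjusting for potential confounders and maintaining the correlation between costs and effects". No covariates are listed there. The ICER is formed by "dividing the mean difference in total societal costs by the mean difference in effects".

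The only covariates named anywhere in the article are under Statistical analyses, for the mixed-model effect analyses: "Adjustments will be made for possible confounders such as gender, age and education level". No baseline value of any outcome appears among them.

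Under Randomisation, allocation uses "a block size of 4, a random cell selection a 1:1 allocation ratio". No balancing on utility is described.

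**The concern.** With an area under the curve that starts at time zero, the baseline utility is a component of the outcome. It also predicts the later utilities that make up the rest. The programme cannot have caused a difference between arms at baseline, yet in an analysis without baseline adjustment part of that difference appears in the QALY contrast.

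The stated reason for adjusting is confounding, illustrated by demographic variables. Baseline utility is needed for another reason: it is part of the outcome and strongly prognostic for the remainder. An analyst could follow the text faithfully, adjust for gender, age and education, and leave it out.

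The QALY difference is the denominator of the cost-utility ICER and feeds the acceptability curve. If the true difference over 9 months is small, a chance shift of the size worked out below could change its magnitude or its sign.

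**Working it through.** The article gives no utility SD, no between-visit correlation and no expected QALY difference, so there is no figure of its own to reproduce.

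**Inputs from the article.** Utilities at 0, 3, 6 and 9 months; linear transitions; 156 patients randomised 1:1, so 156 / 2 = 78 per arm.

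**Assumptions, not in the article.** Utility SD 0.20 (range 0.15 to 0.25), equal at all visits. The same correlation ρ between any two visits, 0.6 (range 0.5 to 0.8, with 0 as a floor). Clustering by pharmacy and the demographic covariates are ignored.

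**Step 1: weights.** With visits 0.25 years apart, the trapezium rule gives QALY = 0.125·u0 + 0.25·u3 + 0.25·u6 + 0.125·u9. The weights sum to 0.75. The baseline share is 0.125 / 0.75 = 1/6.

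**Step 2: carry-over.** The slope of QALY on baseline utility is 0.125 + (0.25 + 0.25 + 0.125)·ρ = 0.125 + 0.625·ρ. Full carry-over would be 0.75.

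**Step 3: size of a chance imbalance.** The standard error of the baseline difference is SD·√(2/78). At SD 0.20 this is 0.20 × 0.160 = 0.032. An imbalance at least this large, in either direction, occurs in about 32% of trials.

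**Step 4: precision.** The QALY variance is SD²·[0.15625 + 0.40625·ρ], where 0.15625 is the sum of squared weights and 0.40625 = 0.75² − 0.15625. R² of QALY on baseline is slope² divided by the bracket. The adjusted standard error is the unadjusted one times √(1 − R²).

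Results at SD 0.20 and 78 per arm:

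| ρ | Slope | Shift per 1-SE imbalance | R² | SE unadjusted | SE adjusted | Reduction |
|---|---|---|---|---|---|---|
| 0 | 0.125 | 0.004 | 0.10 | 0.0127 | 0.0120 | 5% |
| 0.5 | 0.4375 | 0.014 | 0.53 | 0.0192 | 0.0131 | 32% |
| 0.6 | 0.50 | 0.016 | 0.625 | 0.0203 | 0.0124 | 39% |
| 0.8 | 0.625 | 0.020 | 0.81 | 0.0222 | 0.0096 | 57% |

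**Range of the shift.** Low end (SD 0.15, ρ 0.5): 0.024 × 0.4375 = 0.0105. High end (SD 0.25, ρ 0.8): 0.040 × 0.625 = 0.025. With 60 per arm, the group size in the article's sample size calculation, the range is 0.012 to 0.0285.

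**After the fix.** With baseline utility in the QALY equation, the expected carry-over is zero.

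**The case against.** The strongest objection is that no error is on the page. The Economic evaluation section promises an adjusted regression and lists no covariates. The named covariates belong to a different analysis and are introduced as examples. Baseline utility is collected and prognostic, so it is a natural candidate, and nothing rules it out. A condensed article commonly leaves exact covariates and the imputation model to a full analysis plan, which is not shown here.

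Much of this stands, and it rules out three stronger readings that a reader might infer:

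- **That baseline utility is excluded from the adjustment set.** The article fixes no closed set, so this cannot be said.
- **That the QALY estimate is biased.** Allocation is randomised, so the unadjusted contrast is unbiased over repetitions, and the planned bootstrap intervals already reflect that sampling variability. What remains is imbalance conditional on the baseline actually observed, and lost precision.
- **That an imbalance enters in full.** Only 0.125 of a baseline difference enters mechanically. The total of 0.44 to 0.63 depends on assumed correlations of 0.5 to 0.8.

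The area-under-the-curve method is also sound in itself. The wording to amend is the adjustment rule.

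The objection does not remove the point. The article does state an adjustment rule, in a section detailed enough to fix the imputation method and the number of bootstrap replications. That rule selects covariates for a reason that need not lead to baseline utility. Leaving the choice open until the data are seen would also leave the ICER open to analyst discretion.

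**Conclusion.** The point holds in a limited form: the stated rule permits adjustment for baseline utility but does not secure it, and leaving it out would give a poorer QALY estimate than the collected data allow.

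The cost of omission is conditional. It arises only if baseline utility is not among the covariates finally used, and its size rests on the assumed SD, correlations and compound symmetry. Within those ranges a one-standard-error imbalance moves the QALY difference by about 0.011 to 0.025, and about a third to just over half of the standard error could have been avoided. At a correlation of zero the effect would be slight.

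This concerns a secondary economic result. It does not touch the MARS-5 primary effect analysis or the validity of the trial. It merits a change because the improvement is concrete and uses data already collected.

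**What to change.** In the Economic evaluation section, or the corresponding part of the full analysis plan, state that the main bivariate regression includes baseline EQ-5D-5L utility as a covariate in the QALY equation, and baseline MARS-5 in the effect equation when the effect is adherence. Keep the other planned confounders. Include both baseline values in the MICE imputation model.

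The cost is one covariate per equation and a sentence or two of text. Both instruments are already administered at baseline, and the bootstrap and ICER steps stay as they are. If the full plan already specifies this, the sponsor need only confirm it.

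The area-under-the-curve description under Quality of life needs no change.
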